## Abstract

**Background:**

A birth companion is a simple and low-cost intervention that can improve both maternal and newborn health outcomes. The evidence that birth companionship improves labor outcomes and experiences of care has been available for many years. Global and national policies exist in support of birth companions. Many countries including Ethiopia, Kenya, and Nigeria have not yet incorporated birth companions into routine practice in health facilities. This paper presents the protocol for a trial that aims to assess if a package of interventions that addresses known barriers can increase the coverage of birth companions.

**Methods:**

This two parallel arm cluster randomized controlled trial will evaluate the impact of a targeted intervention package on scale-up of birth companionship at public sector health facilities in Ethiopia (five study sites encompassing 12 facilities), Kenya (two sites encompassing 12 facilities in Murang’a and 12 facilities in Machakos counties), and Nigeria (two sites encompassing 12 facilities in Kano and 12 facilities in Nasarawa states). Baseline and endline assessments at each site will include 744 women who have recently given birth in the quantitative component. We will interview a maximum of 16 birth companions, 48 health care providers, and eight unit managers quarterly for the qualitative component in each country.

**Discussion:**

Ample evidence supports the contribution of birth companions to positive health outcomes for mothers and newborns. However, limited data are available on effective strategies to improve birth companion coverage and inform scale-up efforts. This trial tests a birth companion intervention package in diverse clinical settings and cultures to identify possible barriers and considerations to increasing uptake of birth companions. Findings from this study may provide valuable evidence for scaling up birth companionship in similar settings.

**Trial registration:**

Trial is registered with ClinicalTrials.gov with identifier: NCT05565196, first posted 04/10/ 2022.

## Background

Ethiopia, Kenya, and Nigeria have experienced large increases in facility deliveries in the past decade. In Ethiopia, facility births increased from 11% to 2011 to 48% in 2019, in Kenya from 43% to 2008 to 61% in 2014 and in Nigeria from 23% to 2013 to 40% in 2018 [1–6]. As the volume of facility births increase, improving and ensuring quality maternity care has become a focus area for the Ministries of Health in Ethiopia, Kenya, and Nigeria [7–9].

The presence of a birth companion during a woman’s labor and birth is a simple and low-cost intervention that can improve both maternal and newborn health outcomes. This kind of support has been referred to by several different names: companion of choice at birth; continuous support during childbirth, labor companion, and emotional support during birth [10]. A birth companion can provide emotional support by continuously being present and by giving praise and reassurance; provide information on how the labor is progressing; provide coping techniques such as breathing appropriately; give comfort such as massage; assist in mobility; give reminders to drink fluids and visit the restroom; advocate on behalf of the woman; and engage in caring for the newborn [11–13].

A 2013 Cochrane systematic review of 21 trials showed that women who had continuous presence and support during labor or labor and birth were more likely to have a spontaneous vaginal birth, and report satisfaction with the care they received. Having continuous support during labor was also associated with shorter labor, reduced need for pain medication during labor, and lower likelihood of having a caesarean delivery or instrumental vaginal birth. Continuous support was also associated with lower rates of depression and improved Apgar scores of the newborn [11].

The evidence that birth companionship improves labor outcomes and experience of care has been available for many years. As such, global guidance supports birth companions. The World Health Organization (WHO) states “continuous companionship during labor and childbirth is recommended for improving women’s satisfaction with services;” [14] and a companion of choice is recommended for all women throughout labor and childbirth [15]. The WHO quality of care framework also states that a woman should have access to the social and emotional support of her choice [16]. National polices in Ethiopia, Kenya, and Nigeria support birth companions. However, birth companions are not yet incorporated into routine practice, and women typically labor and give birth alone [11, 12, 17–23]. One study in Ethiopia showed that 98% of women were not allowed to have a birth companion, and another study in Kenya found 78% were not allowed a companion during labor and 84% during delivery [17, 19]. In Nigeria, a study showed that only 29% of mothers experienced companionship during delivery [20].

A 2019 Cochrane review outlined common barriers to facilities adopting birth companionship: health facility policies, provider attitudes, facility infrastructure, and preparation of families and birth companions [24]. Implementation research on birth companions is needed to test interventions in varying clinical settings and cultures that will address these barriers and lead to increased uptake of birth companions in health centers and hospitals. Common barriers identified in the literature that hinder birth companion presence include lack of facility polices, low knowledge of the benefits of birth companionship by providers and families, space and privacy constraints, negative attitudes of providers, and lack of preparedness of families and birth companions [24]. It is unknown whether a health facility’s readiness to change impacts their ability to successfully implement interventions that increase uptake of birth companions [10].

### Birth companion intervention package

This study will evaluate an intervention package of eight elements to increase birth companion coverage based on the framework described in the Cochrane review (Fig. 1) [24]. It will include the following:

*Orient facilities and providers to benefits of birth companionship.* Key individuals (e.g., facility managers, clinical staff) from each intervention facility will be oriented on the benefits of birth companions. We will arrange for a benchmark visit to a facility where birth companions have been incorporated into practice, where possible.*Develop/update formal standard operating procedures (SOPs) for implementing birth companions and plan to implement guideline/SOP*. We will develop a template to be provided to each intervention facility along with an existing SOP that can serve as an example. We will identify individuals in these facilities to participate in the development of a SOP and one person to lead the process. A workshop will be conducted to develop the SOP. Participants will include staff, postpartum women with experience of having a birth companions, and birth companions. The SOP will be finalized and endorsed by the facility director or designee.*Design and complete rapid physical space and assess data needs for audit and feedback cycles*. We will develop a template, which, together with the intervention facility staff, will be used to assess and determine the physical/environmental changes or enhancements that are needed to incorporate or increase use of birth companions (e.g., chairs for companions to sit, more functional privacy barriers). We will then support the facilities to make the necessary changes and procure the required equipment and supplies. We will initially assist facilities to assess their data availability to measure coverage of birth companions as part of facilitating audit and feedback cycles. If additional data is required, we will work with the facility to develop methods to measure coverage and then establish targets.*Develop resources on how to support women and a means to distinguish/recognize the birth companion*. We will assess the available birth companion-related resources and either adapt or develop new materials (e.g., posters, brochures, short video). Job aids for care providers will allow them to communicate the benefits of birth companions to pregnant women and clarify the role of providers and birth companions. For mothers, the resources will promote the presence and importance of birth companions. For birth companions, the materials will explain their role during labor, birth, and the postnatal period. We will also assess the best way to designate the birth companions (e.g., gowns, nametags, stickers) and provide the facilities with the necessary materials.*Prepare providers to integrate birth companions into the care team.* An orientation and planning meeting will be conducted to operationalize the SOP with intervention facility staff working in antenatal care (ANC) clinic and labor and delivery ward (including support staff). Community health workers will also be included so they can raise awareness about the birth companion intervention.*Orient ANC clients to rationale for and selection of a birth companion*. After the launch of the intervention, pregnant women anticipating delivery in intervention facilities will be oriented to birth companions during ANC, optimally during their third trimester ANC visit. Similar information will also be available in the labor ward, ensuring that the information reaches women who did not have a third trimester ANC visit at intervention facilities. Pregnant women who are close to their due date will also be reminded by community health workers in the intervention health facilities’ catchment area to plan on having a birth companion. We will use developed materials to communicate the benefits of birth companion.*Prepare birth companions to support women*. Birth companions in intervention facilities will be oriented using the resources developed (e.g., short video) on their role and how they can best support the woman during labor, birth, and the postnatal period. We will also ensure that birth companions are easily recognizable (e.g., gown, wristband, nametag).*Begin audit and feedback cycle to iterate model and track intervention*. We will support existing facility meetings to review data. Facilities will modify implementation of the package, as needed, to increase coverage. We will capture modifications to the intervention through process documentation.

Use of a birth companion will be voluntary for participants and non-participants who seek care at study site facilities. There are no retention strategies for women or companions for the intervention. Staff at intervention facilities will be supported to implement the package through on-site monitoring and audit and feedback cycle data reviews.

**Fig. 1 Fig1:**
[figure not shown]
Components of the birth companion intervention package of interventions

## Methods

### Aims

To determine the feasibility and acceptability of the birth companion intervention package to increase coverage of birth companions during labor, birth, and the postnatal periods.

### Design and setting

This study will use a two parallel arm cluster randomized controlled trial (cRCT) design stratified by country/county and birth volume, with 12 public health facilities in Ethiopia, 24 public health facilities in Kenya, and 24 public health facilities in Nigeria. This study will be happening in and near Addis Ababa city of Ethiopia, Machakos and Murang’a counties of Kenya, and Kano and Nasarawa states of Nigeria (Tables 1, 2 and 3).

**Table 1 Tab1:** Health facilities in Ethiopia by type of facility and the average number of births per month

Facility #	Average # births/ month	Type of facility ^a, b^
1	327	CEmONC
2	262	CEmONC
3	122	BEmONC
4	91	BEmONC
5	83	CEmONC
6	74	BEmONC
7	46	BEmONC
8	29	BEmONC
9	27	BEmONC
10	20	BEmONC
11	16	BEmONC
12	16	BEmONC

**Table 2 Tab2:** Health facilities in Kenya by county, type of facility, and the average number of births per month Murang’a County

Facility #	Average # births/month	Type of facility ^a, b^
**Machakos**		
1	293	CEmONC
2	194	CEmONC
3	96	CEmONC
4	63	CEmONC
5	48	BEmONC
6	41	CEmONC
7	40	CEmONC
8	39	BEmONC
9	28	BEmONC
10	26	BEmONC
11	18	BEmONC
12	18	BEmONC
**Murang’a**		
1	318	CEmONC
2	287	CEmONC
3	121	CEmONC
4	115	CEmONC
5	106	CEmONC
6	66	CEmONC
7	53	BEmONC
8	32	CEmONC
9	31	BEmONC
10	30	BEmONC
11	28	BEmONC
12	19	BEmONC

^a^ CEmONC: Comprehensive emergency obstetric and newborn care

^b^ BEmONC: Basic emergency obstetric and newborn care

**Table 3 Tab3:** Health facilities in Nigeria by state, type of facility, and the average number of births per month State

Facility #	Average # births/month		Type of facility ^a,b^
**Kano**			
1	260		CEmONC
2	240		CEmONC
3	179		BEmONC
4	177		CEmONC
5	144		BEmONC
6	143		BEmONC
7	48		BEmONC
8	45		BEmONC
9	39		CEmONC
10	38		BEmONC
11	37		BEmONC
12	34		BEmONC
**Nasarawa**			
1	312	CEmONC	
2	300	CEmONC	
3	135	BEmONC	
4	109	CEmONC	
5	69	CEmONC	
6	64	BEmONC	
7	45	CEmONC	
8	41	CEmONC	
9	37	BEmONC	
10	37	BEmONC	
11	37	CEmONC	
12	36	BEmONC	

We will use a mixed methods approach to assess impact of the birth companion intervention package and measure the study outcomes with exit interviews, health facility register data extraction, in-depth interviews (IDIs), focus group discussions (FGDs), and key informant interviews (KIIs).

There are five data collection periods. We will first conduct a baseline assessment over the course of approximately four weeks, in facilities meeting the inclusion criteria. Health facilities that decline to participate in the study will be replaced by another facility. Facilities will be randomized after the baseline survey in a 3:1 ratio (i.e., for every three facilities that implement the birth companion intervention, one will serve as a control facility). Randomization is stratified by the number of facility deliveries and by country (Ethiopia) or by county or state within a country (Kenya and Nigeria). Intervention facilities will prepare to introduce the birth companion intervention package over the course of approximately two months to facilitate the presence of birth companions during labor, birth, and the postnatal period. Control facilities will continue to provide the local standard of routine care which may or may not include a birth companion. Facilities will not be replaced or reallocated to study arm post-randomization. This study does not place restrictions on facilities or participants regarding participation in other interventions or research.

We will have three quarterly quantitative and qualitative data collection periods, each lasting for approximately one week. We will conduct an endline quantitative survey, approximately 12 months after birth companion intervention initiation. Mothers, birth companions, health care providers, and unit managers in study facilities will have the option to decline to participate in the study.

At the end of the study, control facilities will be supported to implement the birth companion intervention package by staff from an intervention facility that has a birth companion coverage of approximately 50% or higher (see Fig. 2), assuming that one is available. We will provide limited technical and material support during this period.

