### Sample size

#### Quantitative

The sample size justification is based on estimating coverage of birth companionship. We assumed a within-facility intra-class correlation coefficient (ICC) between 0.05 and 0.5 (higher is more reasonable). We also assumed post-birth companion support coverage at 50%. Baseline/standard practice birth companion coverage varied between 5% and 20%.

Sample size is calculated separately by country for two-sample comparison of proportions (with pooled Z-test) in a cluster randomized design using PASS (PASS 15 Power Analysis and Sample Size Software (2017). NCSS, LLC. Kaysville, Utah, USA, ncss.com/software/pass) [25].

The calculations below apply to the study area in Ethiopia, the two study counties in Kenya, and the two study states in Nigeria. We assume the same baseline level of birth companion coverage in all three countries. There are the same total number of facilities to be randomized at each study area, n = 12 (three in the standard arm and nine in the intervention arm). There will be a total of 12 facilities in Ethiopia, 24 in Kenya, and 24 in Nigeria.

The number of women per facility and total number of women across the two study arms per study site needed was calculated for at least 80% statistical power to test differences in proportions of birth companion coverage between study arms at 0.05 level of statistical significance, assuming that for every three facilities randomized to the birth companion intervention, one facility will be randomized to the standard practice arm and a coefficient of variation of one. Post-birth companion intervention coverage is assumed to be 50%.

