Conservatively assuming 20% birth companion coverage in the standard practice (control) arm and 50% in the birth companion intervention arm at the endline, to have 80% statistical power to detect this difference in proportions at 0.05 level of statistical significance, coefficient of variation of one, we will need to include 62 women who recently gave birth (on average) at each of the 12 health facilities per study area, for a total of approximately 744 women across the two study arms (186 in control arm, 558 in the intervention arm). In this scenario in each of the study sites (Addis Ababa and surrounding area, Machakos and Murang’a counties, and Nasarawa and Kano states), three facilities will be randomized to the standard arm, and nine facilities to the birth companion intervention arm. Since the coefficient of variation is almost one, based on the facility data presented in Tables 1, 2 and 3, the same sample size is used for considering a varying cluster size. We will include all births occurring within the seven data collection days from all facilities. Thus, we will recruit more births from health facilities with a higher volume of births and fewer from health facilities with smaller volume of births. Randomization of facilities was conducted by the Johns Hopkins Biostatistics Center.

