### Statistical analysis and power

The following methods will be used to describe group characteristics or differences: for categorical variables, the number, and percent in each category; for continuous variables, the mean, median, standard deviation, quartiles, and range (minimum, maximum). Adequacy of the randomization will be assessed at baseline by comparing characteristics of participants and facilities in intervention and control arms, including demographics, birth companion coverage, and experience of care.

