### Trial status

This trial is registered with ClinicalTrials.gov with identifier: NCT05565196, first posted October 4, 2022. This trial is currently recruiting. Baseline surveys were conducted in Ethiopia October 10─November 22, 2022 and in Kenya from November 1─December 9, 2022. For Nigeria, we have received ethical clearance and are preparing to conduct the baseline survey. We anticipate reaching study completion in mid- to late-2024.

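### Facilities are randomised after the baseline survey, but the companion coverage it measures is not used in the draw; if Kano and Nasarawa are still unallocated, a constrained draw would cut chance imbalance at small cost

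*Protocol article*

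**What the plan says.** Under Design and setting, the protocol article states "Facilities will be randomized after the baseline survey in a 3:1 ratio", and "Randomization is stratified by the number of facility deliveries and by country (Ethiopia) or by county or state within a country" (Kenya and Nigeria). No other restriction on the draw is named. Each study area has 12 facilities, "three in the standard arm and nine in the intervention arm" (Sample size, Quantitative).

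The baseline survey measures companion coverage at every facility. Under Statistical analysis and power, the arms are to be compared at baseline on characteristics "including demographics, birth companion coverage, and experience of care". Under Analysis of primary outcomes, the first comparison is a cluster-weighted chi-square test at the end of the intervention. Logistic regression with cluster-correlated standard errors follows if baseline covariates that may affect the outcome differ between arms. That analysis is done separately for each sub-national region.

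On timing, Trial status says: "For Nigeria, we have received ethical clearance and are preparing to conduct the baseline survey". The Sample size section says, without naming a country, that randomisation has been carried out.

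**The concern.** The survey comes before the draw, so each facility's value on the primary outcome is known when facilities are allocated. Past coverage is probably the best single facility-level predictor of later coverage, yet the draw ignores it. With three control facilities in a region, one unusual facility can shift the control mean a long way. Because regions are analysed separately, the shift is not averaged out over the 60 facilities.

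The planned effect is 50% against 20%, or 30 points. A 10-point starting gap is one third of that. To the extent that facility coverage persists from baseline to endline, such a gap can enlarge or mask a regional effect, and it gives readers a ready reason to doubt the result.

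**Working it through.** **Inputs from the protocol.** Three control and nine intervention facilities per region. Baseline coverage 5% to 20%. ICC 0.05 to 0.5, with the higher end called more reasonable. Endline 20% against 50%. 62 women per facility on average, cluster-size coefficient of variation (CV) 1, 80% power, alpha 0.05 (two-sided assumed). Monthly births in Kano and Nasarawa from Table 3. Baseline survey of about four weeks.

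**Assumptions added.** Three volume strata (facilities ranked 1–4, 5–8, 9–12) with one control in each, giving 4 × 4 × 4 = 64 allocations; the article gives no strata or cut-points. True facility coverage follows a beta distribution with variance ICC·p(1−p), unrelated to volume.

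**The plan's own figure first.** Design effect = 1 + ((1 + CV²)m − 1)·ICC. With m = 62, CV = 1 and ICC = 0.05, this is 1 + (124 − 1)(0.05) = 7.15. Effective sizes are 186/7.15 = 26.0 and 558/7.15 = 78.0. The pooled proportion is 0.25(0.20) + 0.75(0.50) = 0.425. The null SE is √[0.425·0.575·(1/26.0 + 1/78.0)] = 0.112. The alternative SE is √[0.16/26.0 + 0.25/78.0] = 0.097. Power = Φ[(0.30 − 1.96·0.112)/0.097] = 79.8%. With CV = 0 and ICC = 0.10, power is 80.1%. So the 62 is reproduced at an ICC of about 0.05 to 0.10. The protocol does not say which value was used.

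**Starting gap, equal facility weights.** Between-facility SD = √[ICC·p(1−p)]. SE of the arm difference = SD·√(1/3 + 1/9) = 0.667·SD. Example at p = 0.20, ICC = 0.10: SD = √0.016 = 0.126, SE = 0.084, P(gap ≥ 10 points) = 2[1 − Φ(0.10/0.084)] = 24%.

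| Mean coverage | ICC 0.05 | 0.1 | 0.2 | 0.5 |
|---|---|---|---|---|
| 20% | 9% | 24% | 40% | 60% |
| 10% | 2.5% | 11% | 26% | 48% |
| 5% | 0.2% | 3% | 12% | 33% |

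These are gaps in true coverage. Observed gaps also carry sampling noise and are somewhat more frequent.

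**Starting gap, weighted by births.** The outcome is a proportion of women and all births in the collection window are recruited, so large facilities count for more. Simulating stratified draws with the Kano and Nasarawa volumes, the chance of a true weighted gap of at least 10 points is:

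| Mean coverage | ICC 0.05 | 0.1 | 0.2 | 0.5 |
|---|---|---|---|---|
| 20% | 16–19% | 33–35% | 48–50% | 64% |
| 5% | 2–3% | 7–9% | 15% | 22–25% |

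**Effect of constraining the draw.** Rank the 64 allocations on observed baseline coverage from about four weeks of births, keep the best-balanced 32 and draw one. At 20% coverage, the chance of a true weighted gap of at least 10 points becomes:

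| Balance measured on | ICC 0.05 | 0.1 | 0.2 | 0.5 |
|---|---|---|---|---|
| Birth-volume-weighted coverage | 1–3% | 6–10% | 18–21% | 41% |
| Unweighted facility coverage | 8–11% | 18–23% | 32–37% | 51–52% |

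Balancing on unweighted facility means gives up much of the gain.

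**The case against.** Stratified randomisation is valid, and nothing in the protocol is contradictory here. Chance imbalance is part of the between-facility variance that the ICC-based sample size and the cluster-weighted test already allow for. The plan also compares the arms on baseline coverage and adjusts when they differ. All of this stands. Its limits are that adjustment is conditional on what the baseline shows, that it rests on three control facilities, and that it loses precision when arm and baseline coverage are correlated across 12 facilities.

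Two stronger readings are tempting. A reader might infer that the arms will often start 10 or more points apart. That is fair at 20% coverage with an ICC of 0.1 or more, but not at 5% coverage with a low ICC, and 5% is within the protocol's own range. In favour of the higher figures, the protocol calls higher ICCs more reasonable, and its Background cites 29% companionship at delivery for Nigeria. A reader might also infer that any gap passes straight into the result. That would need facility coverage to persist almost perfectly from baseline to endline and would ignore the planned adjustment.

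Feasibility can be questioned too. The statement that randomisation was conducted names no country, and completion in mid- to late-2024 leaves little slack after two months of preparation and about 12 months to endline.

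**Conclusion.** The point holds as a cheap improvement to the design. It does not show an error or a bias. The allocation leaves unused a measurement of the primary outcome that is already in hand when the draw is made. In Kano and Nasarawa the chance of a true weighted gap of at least 10 points is about 16–64% at 20% coverage and about 2–25% at 5%, rising with the ICC over 0.05 to 0.5. At the ICCs that reproduce the 62 women per facility (0.05 to 0.10), it is about 16–35% at 20% coverage.

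These figures rest on the assumed three-stratum structure, on the beta distribution, and on coverage being unrelated to volume. If volume predicts coverage, the existing strata already remove part of the gap. That Nigeria is unallocated follows from reading Design and setting together with Trial status, and should be confirmed.

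**What to change.** First confirm that the Kano and Nasarawa facilities have not been randomised. If they have not:

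- Amend Design and setting so that in each of the two states the randomising centre lists all volume-stratified allocations, keeps the half with the smallest between-arm difference in birth-volume-weighted baseline coverage, and draws one at random.
- Amend Analysis of primary outcomes so that facility baseline coverage is a covariate in those two regional analyses, whether or not the arms turn out to differ.
- Leave the Ethiopia and Kenya allocations as they are.

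The cost is a short amendment and a little programming, with no new data collection, since the baseline already precedes the draw. Baseline data must be cleaned before allocation, which matters on a tight timeline. There are fewer admissible allocations, and Nigeria's method will differ from that of the other two countries, which the report should state. A permutation test is optional. If one is used, it should run over the constrained set; with 32 allocations its smallest p-value is 1/32 = 0.03, so only the single most extreme allocation could fall below 0.05.
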